#### **Statistical analysis for sub-studies A-C:**

Depending on the type of endpoint, similar statistical analyses as outlined above for the main study will be performed taking only the patients included in the respective sub study. The main comparison depends on the randomization for a specific substudy. If applicable, it will be investigated whether there is an interaction with the treatments options in the main study ("antiviral" treatment arms)

#### **Sub-study A:**

- Rivaroxaban as anticoagulant 10 mg  $\frac{1}{2}$ -0- $\frac{1}{2}$
- Best standard of care (which will likely include prophylactic doses of low molecular weight heparin).

#### **Sub-study B:**

- RAS blocking agent (Candesartan)
- Best standard of care: non-RAS blocking agents (nitrendipine, amlodipine or doxazosin)

#### **Sub-study C:**

- Best standard of care (without IL-6 blockade), or placebo on top of standard of care
- Asunercept at 25mg, 100mg, 400mg once weekly
- Pentaglobin 7mg/kg bodyweight/day continuous iv infusion over 12 hours for 5 days

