| INVESTIGATIONAL DRUG | 
Treatment arm 1: Hydroxychloroquine 200mg 2-0-2 on day 1 followed by 200mg 1-0-1 for 7 days (recommended, or up to maximum dose of 600mg or 200mg 1-1-1 where standard practice)
 
THIS TREATMENT ARM IS INACTIVE
 
Treatment arm 2: Lopinavir/Ritonavir 200mg/50mg 4-0-4 loading dose, followed by 3-0-3 maintenance dose
 
Treatment arm 3: Remdesivir 200mg on day 1, 100mg/day for <math>\geq 4</math> further days (total treatment <math>\geq 5</math> days, according to locas standard)
 
Treatment arm 4: standard of care (SOC)
 
Sub-study A: Rivaroxaban as anticoagulant 10 mg <math>\frac{1}{2}</math>-0-<math>\frac{1}{2}</math> (or 2.5mg 2-0-2, as available) vs standard of care thromboprophylaxis with low molecular weight heparins (e.g. enoxaparin 40mg)
 
Sub-study B: Candesartan as RAS blocking agent vs standard of care (e.g. nitrendipine, amlodipine or doxazosin as control agents (depending on concomitant medication and comorbidities), dose titrated to normotension.
 
Sub-study C:
 
 
Asunercept, administered once weekly intravenously at 25mg, 100mg or 400mg
 
Pentaglobin, continuous IV application over 12h of a total dose of 7ml/kg/day for 5 days, provided in a 50mg/ml solution
 
 |

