### **Pentaglobin**

1 ml solution of Pentaglobin (Biotest Pharma GmbH) contains 50 mg human plasma proteins, of which at least 95% are immunoglobulin M (IgM, 6 mg), immunoglobulin A (IgA, 6 mg) and immunoglobulin G (IgG, 38 mg). The distribution of the IgG subclasses is approx. 63% IgG1, 26% IgG2, 4% IgG3, 7% IgG4. In the 2015 CIGMA study with BT086, another IgM-enriched immunoglobulin preparation, in severe pneumonia, it was shown for the first time that patients benefit greatly from substitution with IgM. Lethality was significantly reduced in subgroups of patients with low IgM levels or high C-reactive protein levels.

Since immunoglobulins are natural, human proteins, the use of which in this indication has been approved since 1985, the positive benefit-risk ratio is well established.

The increased dose as compared to the product information is due to the critical condition of the patients (SOFA  $\geq$  8). The dosages in the technical information are recommendations and can serve as a guidance. In the studies by Rodriguez et al. (2005) and Welte et al. (2015), the higher doses used here have already been applied successfully.

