## **5.2 Study rationale**

Currently there is no established therapy for SARS-CoV-19 infections. The current protocol is designed as a randomized platform protocol that aims to compare different experimental therapies with each other and with “standard of care” (SOC) to identify the most effective treatment, but also relevant and possibly dangerous side effects, as rapidly as possible. The overarching aim of this trial is to prevent uncontrolled, single-arm trials that are unable to provide information on efficacy or safety for experimental treatments. The current situation of an unexpected pandemic requires a certain degree of flexibility, which was implemented in the study design. Numerous studies are currently being performed and aim at providing evidence for an effective and safe treatment. Companies are simultaneously interested in delivering new medications and new strategies to treat SARS-CoV-2 infection, prevent ARDS or treat ARDS on an almost daily basis. Likewise, treatments may be proven futile and may lead to an early termination of a treatment arm. Other agents may become available and new treatment arms may be added later in the form of substantial amendments. We chose the current design of a platform trial with various treatment arms to be able to respond quickly to these requirements. Noteworthy, the WHO launched a master protocol, which our project is based on (Coronavirus disease, COVID-2019, R&D. Geneva: World Health Organization, [www.who.int/blueprint/priority-diseases/key-action/COVID-19](http://www.who.int/blueprint/priority-diseases/key-action/COVID-19)).

All listed substances are currently being used in the treatment of SARS-CoV-2 or have been shown to be effective under certain experimental conditions. The doses chosen for treatment are the approved doses and the ones recommended by respective guidelines, recommendations etc. As no established treatment is available and most of the substances would be used for treatment of these patients anyway, inclusion of patients into this platform trial does not increase the individual risk of each patient with regards to side effects. However, inclusion of patients into our trial may help to identify the most effective treatment as soon as possible and may help the included patients themselves and future SARS-CoV-2 patients. The trial builds on the hypothesis that “antiviral therapy” may act synergistically with adjunctive or supportive optimization of standard of care.

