#### **Sub-Study C:**

Asunercept

Initial dose: 25 mg, 100 mg or 400 mg

Maintenance dose: same as first dosage, unless other specified by DSMB or interim analysis.

Route of administration: i.v. (in 200 mL NaCl (0.9%))

Duration: up to 4 weeks, treatment will cease when patient can be discharged from hospital (because of significant amelioration) or when patient has deceased.

25mg infusion solution:

For preparation of the infusion solution, 1.25 mL Asunercept (corresponding to 25 mg) is taken from the vial with a syringe and is diluted into the infusion solution. The preparation of the final Asunercept solution for infusion should be performed at room temperature (if possible under aseptic conditions, e.g., laminar flow hood)

100mg infusion solution:

For preparation of the infusion solution, 5mL Asunercept (corresponding to 100 mg) is taken from the vial with a syringe and is diluted into the infusion solution. The preparation of the final Asunercept solution for infusion should be performed at room temperature (if possible under aseptic conditions, e.g., laminar flow hood).

400mg infusion solution:

For preparation of the infusion solution, the complete content of two Asunercept vials (corresponding to 400 mg) is taken with a syringe and is diluted into the infusion solution. The preparation of the final Asunercept solution for infusion should be performed at room temperature (if possible under aseptic conditions, e.g., laminar flow hood).

The total amount of the infusion solution will be approx. 201 – 270 mL depending on the size of the NaCl solution container and the dose of Asunercept.

The IMP solution ready for infusion should be kept at room temperature, and must be applied to the patient within 3 h after preparation (including infusion time).

Asunercept will be administered once per week as an approx. 30 min i.v. infusion in a total volume of approx. 201 – 270 mL and using a commercial 0.2 µm in-line-filter (0.22 µm nominal pore size).

If the weight of a patient is below 50 kg and 400 mg per dose are applied, the infusion time needs to be increased and Asunercept must be administered as an approx. 45 min i.v. infusion.

For safety reasons, patients will be closely monitored throughout infusion. In case of an allergy or incompatibility reaction during infusion, infusion should be stopped and the event must be documented in the CRF.

For Pentaglobin:

dose: continuous IV application of a total dose of 7ml/kg/day

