Route of administration: continuous iv infusion over 12h

Duration: 5 days

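### The Pentaglobin dose is given in ml/kg in the synopsis and dosing section but in mg/kg in the statistical section, a 50-fold difference at the protocol's own concentration

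*Protocol*

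**What the plan says.** The Pentaglobin regimen appears in three places in the current protocol text.

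- **Synopsis, investigational drug row:** "Pentaglobin, continuous IV application over 12h of a total dose of 7ml/kg/day for 5 days, provided in a 50mg/ml solution".
- **Section 8.1.1, Sub-Study C:** "dose: continuous IV application of a total dose of 7ml/kg/day", followed by "Route of administration: continuous iv infusion over 12h" and a duration of 5 days.
- **Section 11.6.2, list of sub-study C treatments:** "Pentaglobin 7mg/kg bodyweight/day continuous iv infusion over 12 hours for 5 days".

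The Pentaglobin paragraph of section 5.1 gives the composition as 50 mg of plasma protein per ml, made up of IgM, IgA and IgG.

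Two further statements concern the reason for the dose. Section 5.1 says "The increased dose as compared to the product information is due to the critical condition of the patients" and adds SOFA of at least 8 in brackets. Section 5.2, speaking of the trial substances together, says "The doses chosen for treatment are the approved doses"; the sentence then goes on to include doses that guidelines and similar recommendations support.

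**The concern.** The numeral, the daily infusion time and the number of days are the same in all three places, and only the unit changes. The passages therefore describe one regimen in two incompatible ways, not two regimens.

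What is at stake is mainly patient safety. Pentaglobin recipients are ICU patients, and section 13.1 allows consent to be waived in sub-study C when the patient cannot give it, so some patients could not query what they are given. Section 9.1.1.7 lists haemolysis, thromboembolic reactions, acute kidney failure and transfusion-associated lung injury among the known risks. A unit error is also easy to miss, because the per-patient number is the same in both units: at an assumed 70 kg, either reading gives 490, once in ml and once in mg.

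The secondary concern is that the stated reason for the dose does not match the population described by the criteria, or the general statement about doses in section 5.2.

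**Working it through.** **Inputs**

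- Volume dose: 7 ml/kg/day (synopsis; section 8.1.1).
- Mass dose: 7 mg/kg/day (section 11.6.2).
- Concentration: 50 mg/ml (synopsis; section 5.1). The components in section 5.1 agree: 6 + 6 + 38 = 50 mg/ml.
- Duration: 5 days in all three places.
- Body weight: not fixed by the protocol. I assume 70 kg, with 50 and 100 kg as a range.

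**Can the section 11.6.2 figure be reproduced from the other two passages?**

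Mass dose = volume dose × concentration = 7 ml/kg × 50 mg/ml = 350 mg/kg/day. Section 11.6.2 states 7 mg/kg/day, so the figure is not reproduced. Ratio = 350 / 7 = 50.

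In the other direction, 7 mg/kg ÷ 50 mg/ml = 0.14 ml/kg/day, against 7 ml/kg/day.

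**Does counting only immunoglobulin close the gap?**

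Section 5.1 says at least 95% of the protein is immunoglobulin. At that minimum, 350 × 0.95 = 332.5 mg/kg/day, and 332.5 / 7 = 47.5. It does not.

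**Whole course**

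350 × 5 = 1,750 mg/kg against 7 × 5 = 35 mg/kg.

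**Per patient per day**

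| Assumed weight | Read as 7 ml/kg/day | Read as 7 mg/kg/day |
|---|---|---|
| 50 kg | 350 ml = 17,500 mg | 350 mg = 7.0 ml |
| 70 kg | 490 ml = 24,500 mg | 490 mg = 9.8 ml |
| 100 kg | 700 ml = 35,000 mg | 700 mg = 14.0 ml |

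The ratio is 50 at every weight, so the assumption about weight affects only the absolute amounts.

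**Secondary point, passages side by side**

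- Section 5.1 ties the increased dose to SOFA of at least 8.
- For Pentaglobin, the inclusion criteria (synopsis; section 7.1.2) ask for a need for oxygen or ventilatory support, CRP above 5 mg/dL and ICU admission. Neither these nor the exclusion criteria (synopsis; section 7.1.3) set a SOFA threshold.
- In section 6.2 and the synopsis endpoint list, modified SOFA is an outcome measure. An ICU patient with SOFA below 8 can therefore be enrolled, although the stated reason for the dose does not cover that patient.
- Section 5.1 says this dose exceeds the product information. Section 5.2 makes no exception for it.

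**The case against.** The strongest reply is that the entry in section 11.6.2 is one line in a list of comparison groups, not an instruction for giving the drug. The administration instruction is section 8.1.1, it agrees with the synopsis, and nothing in the protocol suggests that a site or pharmacy would dose from the statistical section. Section 11.6.2 also says the main comparison follows the randomization, so the groups to be analysed do not depend on this line. All of that stands. It reduces the likelihood of an error at the bedside, but two incompatible doses for one arm remain in the same approved document.

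A reader might infer that the conflict makes the per-protocol analysis of this arm unworkable. The documents do not support that. Section 11.1 excludes only major violations that could affect evaluation of the primary objective, section 11.6.1 makes the per-protocol analysis supportive, and section 11 promises a separate analysis plan for sub-study C, which can define compliance.

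A reader might also infer that the criteria select the wrong patients for this dose. That goes too far. ICU admission, raised CRP and respiratory deterioration do select seriously ill patients; what is missing is the particular SOFA cut-off that section 5.1 uses as its reason. Section 5.1 also points to earlier studies using such doses, and it does not rest its benefit-risk statement on SOFA.

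Similarly, section 5.2 should not be read as a flat claim that this dose is licensed. The sentence covers the whole platform and extends to guideline-recommended doses. It is loose wording, and the tension with section 5.1 is a matter of clarity.

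Finally, the word increased in section 5.1 may tempt a reader to decide which unit was meant. The protocol does not give the product-information dose, so it cannot settle the question by that route.

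**Conclusion.** The contradiction is real and must be corrected. Current text gives the same Pentaglobin regimen as 7 ml/kg/day in two places and 7 mg/kg/day in a third. At the protocol's own 50 mg/ml, that is 350 against 7 mg/kg/day, a factor of 50 (47.5 if only the guaranteed immunoglobulin fraction is counted). The factor needs no assumption from outside the protocol.

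This is an inconsistency of units, not an error in any calculation the trial reports: sample size, power and alpha are untouched. Its weight comes from being the dose of an intravenous product for ICU patients. It may be a simple slip, but the protocol does not say so, and agreement between two of the three passages does not decide which is right.

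The mismatch between the SOFA-based reason, the eligibility criteria and the general dose statement is also present in the text. It is secondary and would not by itself call for urgent action.

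**What to change.** 1. Reconcile the synopsis, section 8.1.1 and the sub-study C list in section 11.6.2 to one dose in one unit. The sponsor must determine what was intended and confirm it; no dose is proposed here.
2. In the same amendment, reconcile the SOFA-based explanation in section 5.1 with the eligibility criteria in the synopsis and sections 7.1.2 and 7.1.3, and with the general statement on doses in section 5.2.
3. Notify sites and hospital pharmacies of the correction to the dose text.

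The cost is a short text amendment and a notice. No recalculation or change to the analysis is needed.

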### **11.6.3 Safety and tolerability endpoints**

- Cumulative incidence of serious adverse events
- Discontinuation or temporary suspension of therapy
- Changes in white cell count, hemoglobin, platelets, creatinine, glucose, total bilirubin, alanine aminotransferase (ALT), aspartate aminotransferase (AST) over time
- Occurrence of drug induced liver injury (DILI) in various treatment arms
- Bleeding events

### **11.6.4 Baseline parameters and concomitant medications**

Baseline parameters, medical history and concomitant medication will be documented during screening and throughout the trial until day 29.

Enrolment, protocol deviations and discontinuations from the study drug and the study will be summarized. Demographics (age, race, ethnicity and sex) and medical history and study drug

administration will also be summarized by treatment group. This will be done for separately for the main study and each sub-study.

For qualitative variables (e.g. sex), absolute (n= ) and relative frequencies will be calculated per treatment group. Data will be visualized by bar plots. For quantitative data (e.g. age), the number of valid observations (n = ), mean, standard deviation, standard error, median, minimum and maximum will be calculated for each treatment group and each time point separately. Data will be visualized by boxplots and histograms.

## 11.7 Interim analysis

After inclusion of 20\* and 50 patients in a treatment arm an interim analysis will be performed. In case of safety or results indicating futility, treatment arms may also be closed at this step.

The first interim analysis is mainly for safety and futility only (\* Note that the first interim analysis will be triggered if at least 2 treatment arms have recruited 20 patients each). In the second interim analysis a sample size reassessment might be performed. To account for the sample size re-assessment, the stagewise p-values using the inverse normal combination function will be used (79-81). To allow for early stopping in case overwhelming effects are observed, an alpha spending function with O'Brien and Fleming (OF) boundaries will be used using a two-sided alpha of 5%. Further details will be provided in the charta of the DMC. Importantly, the interim analyses will not cause a stopping of the trial and will be conducted after patients have been included for two weeks.

## 11.8 Software program(s)

All statistical analyses will be conducted with statistical software like SAS 9.4. (or higher) and R 3.6.3. (or higher).

## 12 DOCUMENTATION AND DATA MANAGEMENT

### 12.1 Documentation of study results

A subject screening and identification Log will be completed for all enrolled subjects with the reasons for exclusion.

#### 12.1.1 Case report form (CRF)

ECRFs will be used for this trial, as provided by the KKS (Koordinationszentrum Klinische Studien).

For each subject enrolled, regardless of study drug initiation, a CRF must be completed and signed by the Investigator or a designated sub-Investigator. This also applies to those subjects who fail to complete the study. If a subject withdraws from the study, the reason must be noted on the CRF. Case report forms are to be completed on an ongoing basis.

If screening failures should not be documented in the CRF, this has to be clearly defined in the protocol. CRF entries and corrections will only be performed by study site staff, authorized by the Investigator.

In a paper based CRF all forms should be completed and must be legible. Entry errors have to be corrected according the ICH-GCP Guidelines.

The entries will be checked by trained personnel (Monitor) and any errors or inconsistencies will be checked immediately.

The monitor will collect original completed and signed CRFs at the end of the study. A copy of the completed and signed CRFs will remain on site, while the original data are handed out to the sponsor.

#### 12.1.2 Data collection

Data collected at all visits are entered into an interactive form. The CRFs will be source documents verified following guidelines established before study onset as detailed in the Monitoring Plan. Maintenance of the study database will be performed by KKS.

### 12.2 Safekeeping

The Investigator will maintain adequate and accurate records to enable the conduct of the study to be fully documented and the study data to be subsequently verified (according to ICH-GCP "essential documents"). These documents will be classified into two different categories: Investigator's study site file (ISF) with all essential documents regarding the study conduct, and subject clinical source documents.

The Investigator's file will contain all essential documents listed in ICH-GCP Guidelines section 8.

Subject clinical source documents include all patient hospital clinical records in original version, such as original laboratory reports, ECG, X-ray prints and other reports.

These two categories of documents must be kept on file by the Investigator for as long as needed to comply with the regulatory requirements.

## 12.3 Quality control and quality assurance

### 12.3.1 Periodic Monitoring

According to GCP at least 3 monitoring visits are scheduled. An initiation visit, one routine visit and a close out visit after the last patient has finished the study or data base lock .

The designated monitor will contact and visit the Investigator on a regularly basis and will be allowed to have direct access to all source documents needed to verify the entries in the CRFs and other protocol-related documents provided that subject confidentiality is maintained in agreement with local regulations. It will be the monitor's responsibility to inspect the CRFs at regular intervals according to the monitoring plan throughout the study, to verify the adherence to the protocol and the completeness, consistency and accuracy of the data being entered on them.

Monitoring will be performed by the KKS.

3 visits/site are planned, only primary endpoint data will be reviewed.

### 12.3.2 Audit and inspections

Upon request, the Investigator will make all study-related source data and records available to a qualified quality assurance auditor mandated by the sponsor or to competent authority inspectors. The main purposes of an audit or inspection are to confirm that the rights and welfare of the subjects have been adequately protected, and that all data relevant for assessment of safety and efficacy of the investigational product have appropriately been reported to the sponsor.

## 12.4 Reporting and publication

### 12.4.1 Publication of study results

The findings of this study will be published by the sponsor (Investigators) in a scientific journal and presented at scientific meetings. The manuscript will be circulated to all co-Investigators before submission. Confidentiality of subjects in reports/publications will be guaranteed.

## 13 ETHICAL AND LEGAL ASPECTS

### 13.1 Informed consent of subjects

Following comprehensive instruction regarding the nature, significance, impact and risks of this clinical trial, the patient must give written consent to participation in the study.

During the instruction the trial participants are to be made aware of the fact that they can withdraw their consent – without giving reasons – at any time without their further medical care being influenced in any way.

In addition to the comprehensive instructions given to the trial participants by the Investigator, the trial participants also receive a written patient information sheet in comprehensible language, explaining the nature and purpose of the study and its progress.

The patients must agree to the possibility of study-related data being passed on to relevant authorities. The patients must be informed in detail of their obligations in relation to the trial participants insurance in order not to jeopardize insurance cover.

Substudy C: in this part of the trial also patients with severe dyspnea and possibly acute respiratory distress syndrome, who may be mechanically ventilated, are eligible. Hence, obtaining informed consent for participation in the trial may not be possible and informed consent may be waived. All subjects will be informed about their participation as soon as possible.

